### Site selection and eligibility

We will implement the EBPs at 16 primary care sites, targeting those with high ambulatory care-sensitive hospitalization rates. Each site will be implementing a single EBP. Implementation strategies are randomized by site. Site implementation consists of four overlapping cohorts of four sites (three randomized to LC and one to IC); all will undergo 18-months of RIVET facilitation (see Figure#1). Time periods without active implementation will serve as the usual care periods for EBQI strategies. Usual care sites will receive Office of Primary Care educational campaigns and dissemination of tools for high-risk patients among primary care teams. VHA regional leaders or VHA facility leaders will select the EBP for primary care sites to implement.

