#### EHR Administrative data

VHA CDW contains data on patient characteristics, outpatient encounters, provider types for each encounter, acute and inpatient care utilization, medication fill history, and Healthcare Effectiveness Data and Information Set (HEDIS) quality metric status. Health factor administrative data is generated by templates constructed for each EBP within the EHR. Managerial Cost Accounting (MCA) data will be utilized for the cost analyses.

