## Outcomes and data analyses

To analyze our primary outcome, receipt of each EBP among top 10th percentile high-risk patients during the 18-month implementation period (Reach), we will model uptake of both practices in our Concurrent Stepped Wedge Design as a multilevel hierarchical model with a repeated cross-sectional data structure in which sites are followed over time. In this design, the data structure includes patients at level 1 (where Reach, the main outcome of interest, in measured), nested within time at level 2, and nested within sites at level 3. The main predictors will be site implementation strategy assignment (EBQI-IC vs. EBQI-LC vs Usual Care) over time (measure as the number of quarter). We will first describe differences in trends using unadjusted analyses, then add covariates for patient characteristics (i.e., age, sex, Elixhauser comorbidity score [66]) and site-level covariates (i.e., number of unique patients served in primary care, rural vs urban). Secondary analyses of Reach will include models by key patient subgroups, including those hospitalized in the 90 days prior to the quarter examined, and models with an interaction term for assigned implementation strategy by EBQI fidelity level (as defined above), to examine how implementation strategy fidelity may have impacted Reach.

To analyze our secondary outcomes of care processes, patient experiences, provider experiences, and performance measures (Effectiveness), we will first model unadjusted trends in outcomes over time for each EBP, by site implementation strategy assignment. We will then model outcomes using two or three-level (depending on whether the metric is measured at the patient or site level) hierarchical models based on the concurrent Stepped Wedge Design using repeated cross-sectional data, adjusted for the same covariates included in the models for our primary outcome. In models of medication adherence, we will add covariates for medication regimen complexity, as indicated by total number of classes of medication prescribed for the condition of interest, and patient co-pay status. If we find differences in outcomes, we will perform mediation analyses that consider how Reach and EBP fidelity may have mediated outcomes [67].

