### Return-On-Investment (ROI) Analyses

We will conduct a budget impact analysis to inform the sustainability of each EBP. Following the VHA recommendation to evaluate cost of projects [70], we will identify the relevant costs associated with implementation of the EBP, the EBP itself, and the consequences of the EBP (e.g., healthcare utilization). Using a micro-costing approach [71], we will collect costs for EBQI-IC and EBQI-LC sites, measuring: 1) implementation costs as one-time costs to develop the intervention; and 2) intervention and downstream costs as costs that would be incurred by facilities adopting the EBPs (e.g., site participants; RIVET implementation team members’ time spent in training, meetings and preparing for meetings; staff time performing the intervention). To capture RIVET implementation team staff time spent in various implementation activities, data will be collected through the implementation facilitation log, administrative documents, and weekly time surveys. For both EBPs, clinical staff will document the estimated time spent to complete EBP through an EHR template. Finally, we will identify the costs of healthcare utilization which may be impacted by the implementation of these EBPs from the VA administrative data, such as change in outpatient utilization (e.g., primary care, social work, mental health, pharmacy) and inpatient utilization. This will be done by estimating the excess cost for patients exposed to the EBP compared to a control group of unexposed patients using multivariable regression models to control for measured confounders. We will use generalized linear models for continuous data and two-part models for semi-continuous data with distributional families chosen to best fit the data. If preliminary data reveals that medication adherence changed with MAA implementation, we will also include changes in pharmacy costs.

We will measure whether EBPs were maintained during each sites’ sustainment period (time period following the 18-month active implementation period), how EBPs spread within the original sites and to new sites, and what factors are associated with maintenance and spread. We will also assess adaptations made to the EBPs in response to changing VHA context.

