For sustainment and spread, we will continue to assess receipt of each EBP among top 10% CAN score patients (Reach) longitudinally during the sustainment period by measuring 6 and 12 months after the active implementation phase. We will incorporate Adoption measures to assess spread within the implementation site and in new sites by measuring how many additional staff were trained on each EBP, proportion of staff trained on each EBP, and which types of healthcare staff delivered each EBP (representativeness). We will compare EBQI-IC and EBQI-LC sites to determine which implementation strategy is most effective for sustaining the EBPs. Using the matrix analysis approach described above, we will analyze qualitative interview data to explore the role of contextual factors on sustainment, and the “fit” between context, intervention, and implementation strategy on sustainability.

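### As worded, usual care includes post-facilitation quarters; if these enter the Reach model as controls and uptake persists, the contrasts are biased

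*Protocol article*

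**What the plan says.** Under Site selection and eligibility, the protocol article describes "four overlapping cohorts of four sites (three randomized to LC and one to IC); all will undergo 18-months of RIVET facilitation". The same paragraph then gives the control rule: "Time periods without active implementation will serve as the usual care periods for EBQI strategies".

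Under Outcomes and data analyses, the primary outcome is "receipt of each EBP among top 10th percentile high-risk patients during the 18-month implementation period (Reach", and the exposure in the model is "site implementation strategy assignment (EBQI-IC vs. EBQI-LC vs Usual Care) over time (measure as the number of quarter". There are three states. None is for time after facilitation.

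The Return-On-Investment section describes the later time as the "sustainment period (time period following the 18-month active implementation period". It adds that "we will continue to assess receipt of each EBP among top 10% CAN score patients (Reach) longitudinally during the sustainment period", at 6 and 12 months, and that IC and LC sites will be compared on how well they sustain the practice.

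Receipt is taken from documentation in the electronic record. Under EHR Administrative data: "Health factor administrative data is generated by templates constructed for each EBP within the EHR".

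**The concern.** Cohorts overlap and each has a fixed 18 months. With any stagger, the first cohort finishes while later cohorts are still active. Its later quarters have no active implementation, so the written rule makes them usual care. Yet these sites have a trained champion and a working EBP template, and the article intends to measure lasting uptake in exactly those quarters. The same site-time cannot be both untreated control and the place where a persisting effect is measured.

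If those quarters are coded as controls, two things follow. The reference condition rises with sustained uptake, so the EBQI-versus-usual-care contrast on the primary outcome is pulled toward zero. And because each site is compared partly with its own post-facilitation quarters, the strategy that sustains better loses more of its apparent effect. That reaches the IC-versus-LC question, which is the purpose of the trial. The article gives a reason to expect unequal retention: its Individual Consultation section cites literature linking IC to better sustainability.

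**Working it through.** **Figures in the article.** It states no power, effect size or expected Reach, so there is none to reproduce. The design figures agree: 4 cohorts × 4 sites = 16 sites (12 LC, 4 IC), and 18 months = 6 active quarters.

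**Reading the sections together.**
- Sustainment is all time after the 18 active months, hence time without active implementation, hence usual care under the control rule.
- No section excludes it, and the three-state exposure offers nowhere else to put it.
- The 18-month window attached to Reach does not settle this. A site's usual-care time always lies outside its own 18 months, so the window applied literally leaves no usual-care quarters. Once it is relaxed to admit controls, the only rule for choosing them is the one that admits sustainment.

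**Illustration.** Assumptions not in the documents: Reach 0% before and 20% during implementation; a fraction *r* of that retained afterwards; cohort starts 2 or 3 quarters apart; 2 baseline quarters; the panel ending when the last cohort finishes, or 2 or 4 quarters later. The model is noise-free least squares on the percentage-point scale, with site and quarter effects and post-facilitation quarters coded as usual care.

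*Pooled EBQI versus usual care.* In a full panel every site has 6 active quarters, so the active indicator adjusted for site and quarter is A minus its quarter mean. Pre, active and post indicators sum to 1, and with equal spacing pre and post are mirror images in time. Each therefore has slope −½ on the adjusted indicator, and

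estimate = 20 × (1 − r/2).

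| Retained *r* | Estimate (points) | Shrinkage |
|---|---|---|
| 0 | 20.0 | 0% |
| 0.25 | 17.5 | 12.5% |
| 0.50 | 15.0 | 25% |
| 0.75 | 12.5 | 37.5% |
| 1.00 | 10.0 | 50% |

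If each site contributes only 2 or 4 post-facilitation quarters, the fits give 17.4–17.6, 14.8–15.3, 12.2–12.9 and 9.6–10.6 at *r* = 0.25, 0.50, 0.75 and 1.00. A linear quarter trend instead of quarter effects gives similar values (50–55% shrinkage at *r* = 1).

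*IC versus LC.* Give both strategies the same true 20 points, but let IC retain 0.75 and LC 0.25. Within a cohort the quarter effects cancel, leaving

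false gap (LC − IC) = 20 × (0.75 − 0.25) × p,

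where p is the post-facilitation share of non-active site-quarters.
- 2-quarter stagger: pre = 4 × (2+4+6+8) = 80 and post = 4 × (6+4+2+0) = 48. So p = 48/128 = 0.375 and the gap is 3.75 points.
- The same with 4 further quarters: post = 48 + 16 × 4 = 112. So p = 112/192 = 0.583 and the gap is 5.83 points.
- 3-quarter stagger: pre = 4 × (2+5+8+11) = 104 and post = 4 × (9+6+3+0) = 72. So p = 72/176 = 0.409 and the gap is 4.09 points. With 4 further quarters, p = 136/240 = 0.567 and the gap is 5.67.

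The false gap is thus about 4 to 6 points. It falls to about 2 to 5 points if each site contributes only 2 or 4 post-facilitation quarters. With equal retention it is zero.

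*After the fix.* With post-facilitation quarters excluded, or given their own term by strategy, every fit returns 20.0 for both strategies and a gap of 0.

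**The case against.** The strongest reply is that the article never says sustainment quarters enter the primary model. It ties Reach to the 18-month period, names sustainment as a distinct phase and gives it its own IC-versus-LC comparison. It also describes usual-care sites as receiving national education and shared tools, which fits sites not yet in the programme better than sites that have completed it. Figure 1, the site timeline, is cited just before the control rule and is not shown, and the SAP is not at hand. All of this stands as evidence about intent. It does not remove the conflict, because the one operative rule says otherwise and the Reach window cannot choose the control quarters.

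Three stronger readings are tempting and are not supported.
- That the primary contrast is biased as a fact. It is biased only if these quarters are used as controls and uptake persists.
- That exactly half of usual-care time is post-facilitation. That holds, for example, with no extra baseline quarters and a window ending at the last cohort's finish. The documents fix neither, and continued use after facilitation is something they plan to measure, not something they assert.
- That a usual-care group of pre-implementation quarters alone would have zero events and break a logistic fit, so usual care should leave the primary test. The article names no link function and does not say pre-implementation Reach is exactly zero. Dropping usual care would discard the planned three-condition comparison and leave 4 IC against 12 LC sites.

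**Conclusion.** The point holds in conditional form. The definition of usual care, followed as written, includes previously facilitated site-time, and the primary model has no state to separate it. This is a stated rule that conflicts with the article's own treatment of sustainment, not a detail left to the SAP. If the rule is applied and uptake persists, the EBQI-versus-usual-care contrast is attenuated, by about 25% at half retention and 37.5% at three-quarters retention in the illustration. Unequal retention also biases IC versus LC against the better sustainer. Direction and mechanism follow from the coding. The sizes depend on the assumed stagger, baseline, Reach and percentage-point scale, and cannot be derived from the documents. There is no bias if Reach returns fully to baseline, or if the analysts already exclude these quarters.

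**What to change.** In Site selection and eligibility, replace the control rule with:

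> Usual care = quarters before a site's implementation start.

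In Outcomes and data analyses, add that quarters after a site's 18 months are either excluded from the primary Reach model or coded as a separate sustainment state by strategy (IC-sustainment, LC-sustainment). Keep the planned IC versus LC versus Usual Care stepped-wedge model, and state which quarters supply the usual-care data, since the 18-month Reach window cannot.

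The cost is a recoded condition variable and fewer usual-care quarters. In particular, no usual-care time remains once the last cohort has started, so that contrast will be less precise and will rest on the earlier calendar quarters. No new data are needed, and the sustainment comparison is unaffected.

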**Methods:**

We will recruit and randomize 16 sites to either EBQI-IC or EBQI-LC to implement one of the EBPs, chosen by the site. Each site will have a site champion (front-line staff) who will participate in 18 months of EBQI facilitation.

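### The primary Reach model pools two leader-chosen EBPs without an EBP term, so an uneven EBP mix among the four IC sites would shift the IC–LC estimate

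*Protocol article*

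**What the plan says.** Under Site selection and eligibility, the protocol article plans 16 sites in "four overlapping cohorts of four sites (three randomized to LC and one to IC"). The randomised element is the strategy: "Implementation strategies are randomized by site". On the practice it says "Each site will be implementing a single EBP" and "VHA regional leaders or VHA facility leaders will select the EBP for primary care sites to implement". The Methods paragraph of the Abstract describes sites randomised "to implement one of the EBPs, chosen by the site". EBP is therefore a site-level factor that is constant within a site, always known and not randomised.

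Under Outcomes and data analyses, the primary analysis is described as follows: "we will model uptake of both practices in our Concurrent Stepped Wedge Design as a multilevel hierarchical model". The main predictors are strategy (IC, LC, usual care) and quarter. The patient covariates are age, sex and Elixhauser score. The remaining terms are "site-level covariates (i.e., number of unique patients served in primary care, rural vs urban"). EBP does not appear for Reach as a predictor, covariate, interaction or subgroup. For the secondary outcomes the same section does describe unadjusted trends separately for each EBP.

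**The concern.** CACP is a multi-domain assessment leading to an individualised treatment plan. MAA is a focused set of questions on taking medication. Their achievable Reach may differ, and nothing in the article says it is equal. With only four IC sites, randomising the strategy alone cannot be relied on to balance the two practices between arms.

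The IC–LC comparison of Reach is the central result of the trial. If the practices differ in Reach and the IC sites lean towards one of them, part of the practice difference is read as a strategy difference. Even with perfect balance, leaving out a strong site-level factor puts its variation into the between-site error. The usual-care periods do not solve this, because EBP never changes within a site and IC versus LC remains a comparison of 4 sites with 12. The Discussion paragraph of the Abstract also promises conclusions that take account of EBP characteristics, which the listed primary model does not do.

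**Working it through.** **Inputs from the article.** Four cohorts × (3 LC + 1 IC) = 16 sites, which reproduces the stated total: 12 LC and 4 IC. Each site has one EBP.

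**Assumptions (not in the article).** An 8/8 mix of CACP and MAA; a CACP–MAA gap in Reach of 5, 10 or 20 points; a between-site SD of 5 or 10 points.

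**1. Chance of an uneven split among the IC sites.**
- Simple allocation, 8/8: P(2:2) = C(8,2)²/C(16,4) = 784/1820 = 43.1%; P(3:1 either way) = 896/1820 = 49.2%; P(4:0 either way) = 140/1820 = 7.7%. Uneven: 56.9%.
- One IC site per cohort, as the article states, with two sites per EBP in each cohort: the number of CACP sites among the four IC sites is binomial(4, ½). P(2:2) = 6/16 = 37.5%; P(3:1) = 8/16 = 50%; P(4:0) = 2/16 = 12.5%. Uneven: 62.5%.
- One EBP per cohort: the IC site always matches its three LC sites, so the imbalance is zero.

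**2. Shift in IC–LC for a given split.** Shift = (CACP share in IC − CACP share in LC) × gap.
- 3:1: 3/4 − 5/12 = 1/3.
- 4:0: 4/4 − 4/12 = 2/3.

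| Assumed gap (points) | 3:1 | 4:0 |
|---|---|---|
| 0 | 0 | 0 |
| 5 | 1.7 | 3.3 |
| 10 | 3.3 | 6.7 |
| 20 | 6.7 | 13.3 |

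These figures weight sites equally. In a stepped-wedge fit the 3:1 figure also depends on which cohort holds the odd IC site.

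**3. Effect on a nominal 5% test.** This used 20,000 simulated 16-site data sets per case, a site-level t-test, no true strategy effect and no EBP term. At 4:0 the false-positive rate for gaps of 5, 10 and 20 points is 15%, 33% and 61% at SD 5, and 8%, 15% and 33% at SD 10. At 3:1 the estimate is shifted, but rejection stays at about 1–5%, because the omitted factor inflates the error. At 2:2 there is no shift, but the test is conservative (0.5% for gap 10, SD 5), which is the loss of precision. Averaged over allocations with two sites per EBP in each cohort, for gaps of 10 and 20 points, the rate is 5.5–8.4%.

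**4. Which term removes the shift.** Receipt is recorded through EBP-specific templates, so a gap would arise mainly once implementation starts. In a simulated stepped wedge (staggered cohorts, quarter effects, site random intercept, usual-care Reach assumed near zero, 20-point gap) the IC–LC bias was:

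| Model | 4:0 | 3:1 |
|---|---|---|
| No EBP term | 13.3 | 5.1 |
| Constant EBP term | 11.6 | 3.9 |
| EBP × active period | about 0 | about 0 |

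A constant term leaves most of the bias, because it forces the same EBP difference on the usual-care quarters.

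**5. Price in precision (site-level approximation).** The squared correlation between IC and EBP is d² × (¼ × ¾)/(½ × ½) = 0.75d², where d is the share difference. The SE factor is 1/√(1 − 0.75d²): 1.00 at 2:2 (d = 0), 1.04 at 3:1 (d = 1/3) and 1.22 at 4:0 (d = 2/3).

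**The case against.** The strongest reply is that the size rests on a gap the article does not give. That stands, which is why a range including zero is shown. Reach counts a partly documented assessment as receipt, which weakens the step from greater effort to lower Reach. The EBQI activities section says the practices share goal, population and setting. That explains why they can sit in one collaborative; it does not say they are equally easy to deliver.

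Second, if the EBP is settled before allocation, the estimator is unbiased over repeated randomisation, and at 3:1, the commonest imbalance, false positives are not inflated. Both points stand. A reader might infer that the strategy comparison is confounded outright; the documents do not support that. The harm is conditional on the allocation obtained, together with lost precision.

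Third, a reader might infer that leaders choose after learning their site's strategy, so that allocation itself influences the EBP. The article is silent on the order, and that silence is no error in a condensed report. Nor is there a serious conflict over who chooses: facility leaders can fairly be called the site, and only choice by regional leaders differs from the Abstract.

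Fourth, the outcome is introduced as receipt of each EBP, which might suggest separate models. The description of a single model for uptake of both practices reads as pooled. Separate models would leave about two IC sites per EBP, or none for one of them at 4:0.

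Finally, covariates are often left to an analysis plan. Here, however, the article gives explicit lists, and EBP is not in them.

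**Conclusion.** The point holds in a conditional form. The listed primary model omits a known, non-randomised site factor that may affect Reach, in a comparison with only four IC sites. Under an 8/8 mix, an uneven IC split has probability 57% with simple allocation and 62.5% with two sites per EBP in each cohort; it cannot occur if each cohort uses one EBP. The resulting shift is one third (3:1) or two thirds (4:0) of whatever CACP–MAA gap exists, and nothing if there is none. Marked inflation of false positives needs the 4:0 split (7.7% or 12.5% under the two allocation assumptions). The EBP mix, the gap and the between-site SD are all assumptions. The plan should be changed because the correction is cheap and the imbalance cannot be ruled out, not because bias has been shown.

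**What to change.** - In the adjusted primary Reach model, add EBP (CACP/MAA) and its interaction with the active-implementation period. A constant site-level EBP term alone is not enough.
- Keep the unadjusted Reach trends without covariates, but present them by EBP, as the article already does for the secondary outcomes.
- Fix and date each site's EBP before its cohort is randomised, and align the Abstract and the site-selection section on who makes the choice.

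The cost is about one site-level degree of freedom for the IC–LC comparison, with its SE larger by a factor of about 1.00 (2:2), 1.04 (3:1) or 1.22 (4:0), plus a dated record of each choice. No new data are needed, because the EBP is known for every site.
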